## **8.7 Drug disposal**

Annually and at the end of the study all packages of medication, whether empty or containing unused drugs collected by study staff, will be disposed of according to local regulatory requirements.

## **8.8 Emergency code breaking**

In the event of a clinical emergency, the participant will be assumed to be taking active therapy and recommended to cease treatment. The code can be broken by contacting the Monash Clinical Informatics and Data Management Unit to handle emergency un-blinding in Australia and the U.S. This procedure will ensure that no-one involved in the management or conduct of the study will have access to the randomization code. Reasons for the un-blinding will be recorded at the Unit and participants will be encouraged to resume their assigned medication if possible after their immediate condition has resolved. Details will be recorded and passed to the ASPREE DMC. The DSMB will also be informed of any emergency code breaks in tabular form. The code will be broken for an individual in the event where knowledge of the precise medication is essential for the clinical management and where this is requested by the treating physician (or the participant). Blinding will be protected by this systematic approach.

## **8.9 Overdose of trial medication**

A procedure in case of overdose with aspirin is to be specified. The signs of acute intoxication of ASA are:

- Mild: Nausea, vomiting, sweating, thirst and tachycardia.
- Severe: Fever, CNS disturbances such as convulsions, hallucinations, coma, and respiratory failure.

*Treatment:* The initial action is to eliminate the swallowed tablets from the gut by gastric washout and administration of activated charcoal for mild cases (i.e. where no depression of conscious state) and transport to a specialized center. Severe cases require emergency transport.

In the event of overdose of study medication, a decision on continuing in the unblinded study will be reviewed. The safety officer may be asked to decide if the patient status is to remain unblinded.

## 9 CONCOMITANT THERAPY

### 9.1 Prescription medications

All prescription medications will be recorded on a *Concomitant Medications* Form including indication for use and start / stop dates. In Australia, family physician records will be checked for the participant's concomitant medications. In the U.S., at study entry and at each annual visit participants will be asked to bring in all of the medications that they currently use or have recently used, including over-the-counter medications (the 'brown bag' method), to verify their current medications.

In addition to prescription medications, any regular use of over-the-counter NSAIDs will also be recorded on the *Concomitant Medications* Form.

## 10 SAMPLE SIZE AND POWER CALCULATIONS

Participants will be approximately two-thirds from Australia and one-third from the U.S and will include 4,500 minority participants. There will be an equal allocation of participants to aspirin and placebo groups. A detailed description of sample size and power calculations for the primary and secondary endpoints is provided in Appendix 2.

In brief, 19,000 participants having 3787 events will be required to have 90% power (two-sided alpha error rate of 0.05) to detect a 10% reduction (risk ratio of 0.90) in the primary endpoint with aspirin. The rationale for this effect size is described in Appendix 2. This sample size was calculated for a univariate Cox proportional hazards regression analysis using Stata (Stata Statistical Software, Release 10, StataCorp, College Station, TX, 2007) and based on the following assumptions:

- a. The effect of aspirin is described by a hazard ratio of 0.90 in an intention-to-treat analysis. This assumes a slightly stronger underlying effect that will be weakened by cross-over of participants for reasons which include the development of a non-fatal, non-disabling cardiovascular or cerebrovascular events necessitating aspirin therapy or cessation (non-compliance) with aspirin therapy. We expect 5% per annum of placebo-group participants to initiate aspirin use (or *vice versa*).
- b. Annual dementia incidence rates of 6 per 1000 for 70-74y age group, 11/1000 (75-79y), 20/1000 (80-84y), 37/1000 (85y+)  for Australian, U.S. Hispanic and U.S. White (non-Hispanic) participants. For U.S. African Americans the rates are doubled .
- c. Incident disability for one or more Katz ADL's; annual incidence rate for males= 19.6/1000, females = 26.5/1000 (these incidence rates are from the rates observed in the subset of

- ASPREE-like participants in the CHS ([name], personal communication, August, 2008) which showed similar rates in U.S. Whites and U.S. minorities).
- d. Age-specific mortality rates in Australian and U.S. White (non-Hispanic) participants are based on the 2004 Australian population census (<http://www.aihw.gov.au/mortality/data>). Age-specific mortality rates in U.S. African American and Hispanic participants are based on 2005 rates specific to each minority (U.S. CDC statistics, 2005; <http://www.cdc.gov/nchs>).
- e. To allow for the analysis to be time-to-first event, individual rates for death, ADL loss and dementia can be summed and the sum reduced by 10% to allow for the potential for different events to occur in the same individual .
- f. Participants will be 45% male and 55% female.
- g. The cohort will consist of 50%, 30%, 15%, 5% in age groups 70-74 years, 75-79 years, 80-84 years, 85 years and over, respectively.
- h. The average at risk time will be 4.25 years per participant which allows for censoring due to the primary endpoint or non-completion of dementia screen or diagnosis, and non-completion of ADLs.

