# 1 INTRODUCTION

## 1.1 Summary

ASPREE is a double-blind, randomized, placebo-controlled primary prevention trial designed to assess whether daily active treatment of 100 mg enteric-coated aspirin will extend the duration of disability-free life in healthy participants aged 70 years and above except for Hispanic and African American minority groups in the U.S. where the minimum age of entry is 65 years. The study will examine whether the potential benefits of low dose aspirin (particularly the prevention of heart disease, stroke, certain cancers and dementia) outweigh the risks (particularly severe gastrointestinal bleeding and hemorrhagic stroke) in this age group.

Participants will be eligible for the trial if they do not have a current clinical indication for (i.e. overt cardiovascular disease) or contraindication to (i.e. allergy or increased risk of bleeding) aspirin, do not have dementia, disability, low hemoglobin levels, or have a condition that is likely to be fatal during the 5 years of the trial and are capable of providing informed consent. Nineteen thousand participants will be required to provide 90% power of a true relative risk benefit of 0.90 for the primary endpoint (a composite of all-cause mortality, incident dementia and persistent physical disability) in an intention-to-treat analysis with an average follow-up of 5 years. The trial has received financial support from the U.S. National Institute on Aging (part of the National Institutes of Health), the National Health and Medical Research Council of Australia, the National Heart Foundation of Australia and the Victorian Cancer Agency. Bayer Pharma AG provides in kind support through the provision of low dose aspirin and matching placebo.

The study will be carried out in community settings in the U.S. and Australia. In the U.S., 2,500 participants will be recruited through clinical trials networks in regional hub settings. In Australia, recruitment of 16,500 participants will take place through general practices with the participant's usual treating General Practitioner (GP) as co-investigator.

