## APPENDIX 2. SAMPLE SIZE & POWER CALCULATIONS

For the primary endpoint, a sample size can be calculated that gives the number of primary endpoint events required for ASPREE to have 90% power for their subsequent analysis by a univariate Cox proportional hazards regression model. To estimate the number of participants required to yield these events, assumptions are made for (i) the event rates that will be seen in ASPREE participants and (ii) the duration of participant follow-up during the study. Having obtained a sample size for the primary endpoint we examine the power or effect size that this number of participants gives us for each secondary endpoint. Hence, assumptions are also required for the event rates of secondary endpoints. In general, Australian event rates have been used as a basis for ASPREE participants. This is justified on the grounds that approximately two-thirds of participants will be recruited in Australia and using the lower Australian rates errs on the conservative side for sample size calculations. For example, Australian rates of all-cause mortality, cardiovascular events and cancer are lower than in the U.S. (see Table 2 of the Research Plan). For the primary outcome, population-specific rates are used where there is strong evidence that a minority group is at increased risk.

The study will have a 1:1 aspirin:placebo group allocation ratio.

All power and sample size calculations were performed with a two-sided alpha error rate of 0.05 for a univariate Cox proportional hazards regression analysis of time to first event using the 'stpower cox' command in Stata (Stata Statistical Software, Release 10, StataCorp, College Station, TX, 2007).

Assumptions used for the original sample size and power calculations include:

- Participants will be 50%, 30%, 15%, 5% in age groups 70-74 years, 75-79 years, 80-84 years, 85 years and over, respectively.
- Participants will be 45% male and 55% female.
- Based on experience with ANBP2, the effect of clustering due to recruitment by country and enrolling general physician or clinical research site will be minimal and no explicit adjustment to the number of participants needs to be made. In any case, since randomization is at the individual participant level, treatment effect is a within-cluster comparison and this protects against any concern over loss of power due to clustering.

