vii. Using the assumptions above, the overall primary endpoint rate in the Australian and U.S. White participants will be 45.4 per 1000 person years, and the event rate in the U.S. minority groups will be 48.9 per 1000 person years.

The study aims for 5 years average follow-up per participant and for the primary endpoint this 'at risk' time for occurrence of a first primary endpoint event will be reduced to an average of 4.25 years per participant. The reasons for this reduction include censoring due to the occurrence of a primary endpoint, loss to follow-up for death (which is expected to be extremely low due to access to mortality statistics through National Death Index records in Australia and U.S), non-completion of dementia screen or diagnosis, and non-completion of ADL's. In total, we assume that 5% of participants per year will have an occurrence of the primary endpoint or have insufficient follow-up to enable assessment of their primary endpoint status.

On the basis of these assumptions, 311 primary endpoint events in 1500 mainly U.S. minority participants and 3374 primary endpoint events in 17,500 Australian and U.S. White participants will yield 89% power (two-sided alpha error rate of 0.05) to detect a 10% reduction (risk ratio of 0.90) in the primary endpoint with aspirin. The final recruitment numbers that were achieved are approximately 16,500 participants in Australia and 2,500 participants in the U.S. Note that this is a variation from the original protocol which specified a plan to recruit 12,500 and 6,500 participants (4,500 from minority populations all aged 70+y) in Australia and the US respectively which had a 90% power.

**The sample size for the primary endpoint of death from any cause or incident dementia or physical disability will be 19,000 participants.**

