### **4. Dementia**

Anticipated rates of dementia are given above under the primary endpoint sample size calculation. A sample size of 19,000 provides 90% power to detect a hazard ratio of 0.807 comparing the aspirin group with placebo in an intention-to-treat analysis (all other assumptions as for primary endpoint).

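### Section 10 still presents the superseded recruitment plan with 3,787 events and 90% power, while Appendix 2 gives 3,685 expected events and 89% power for the current mix

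*Protocol*

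**What the plan says.** **Section 10** describes the cohort as "approximately two-thirds from Australia and one-third from the U.S and will include 4,500 minority participants". It states that "19,000 participants having 3787 events will be required to have 90% power", for a hazard ratio of 0.90 and a "two-sided alpha error rate of 0.05". Its age distribution (item g) and dementia rates (item b) start at 70 years, although Section 6.1 admits African American and Hispanic participants in the U.S. from 65. It refers the reader to Appendix 2 for detail.

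**Section 1.1** says "Nineteen thousand participants will be required to provide 90% power". It already gives the 16,500/2,500 split. It mentions neither 3,787 events nor a two-thirds/one-third mix.

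**Appendix 2, Primary outcome,** expects 311 events in 1,500 mainly U.S. minority participants and 3,374 in 17,500 Australian and U.S. White participants, and says these "will yield 89% power (two-sided alpha error rate of 0.05". It attributes the 12,500/6,500 plan, with 4,500 minority participants all aged 70 or over and 90% power, to the original protocol. The same subsection opens by saying the trial was designed for 90% power, and the opening paragraph of the appendix still puts about two-thirds of recruitment in Australia.

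**Appendix 2, Secondary outcomes,** says for dementia that 19,000 participants "provides 90% power to detect a hazard ratio of 0.807". For all-cause mortality the corresponding figure is 0.842. Both carry over the other assumptions of the primary endpoint.

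**The concern.** Section 10 is current text, not a log of past changes, and it contradicts the appendix it cites on four items: country mix, number of minority participants, the event count attached to 19,000 participants, and power. Someone who reads only Section 10 would expect 19,000 participants to produce 3,787 events. On the protocol's own rates the current cohort falls 102 short of that even if every assumption is met, so a shortfall caused by the change of mix could be mistaken for low event rates. The two secondary hazard ratios also look as though they were left at the old mix when the primary endpoint was re-powered.

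**Working it through.** **Inputs.** Hazard ratio 0.90, two-sided alpha 0.05 (Section 10). Allocation 1:1, rates of 45.4 and 48.9 per 1,000 person-years, and 4.25 years at risk (Appendix 2).

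**1. The stated requirement.** Schoenfeld's formula gives

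E = 4(1.960 + 1.2816)² / (ln 0.90)² = 42.03 / 0.011101 = 3,786.2, rounded up to **3,787**.

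This matches Section 10 exactly.

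**2. Power at each event count.** Power = Φ(½√E × 0.10536 − 1.960).

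| Events | ½√E × 0.10536 | less 1.960 | Power |
|---|---|---|---|
| 3,787 | 3.2419 | 1.2819 | 90.0% |
| 3,685 | 3.1979 | 1.2379 | 89.2% |

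The second line reproduces the 89% in Appendix 2. The gap is 3,787 − 3,685 = 102 events, or 2.7%.

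**3. Yield under the current mix.**
- 17,500 × 0.0454 × 4.25 = 3,377 (stated 3,374)
- 1,500 × 0.0489 × 4.25 = 312 (stated 311)

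Both agree to rounding of the rates.

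**4. What the 45.4 is.** The Australian/White components per 1,000 are:
- dementia: 0.50×6 + 0.30×11 + 0.15×20 + 0.05×37 = 11.15
- disability: 0.45×19.6 + 0.55×26.5 = 23.40
- mortality: half the tabulated rates, weighted by age and sex = 18.51

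The sum is 53.05. Less 10% for overlap it is 47.75 in the placebo arm, and multiplied by (1 + 0.90)/2 it is 45.4. The stated rate is therefore the average of both arms.

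**5. Yield under the original mix.** There were 12,500 Australian and 6,500 − 4,500 = 2,000 U.S. White participants, 14,500 in all, plus 4,500 minority participants. Placebo-arm rates from the Appendix 2 inputs, ages 70 and over, are 64.45 (African American) and 45.58 (Hispanic) per 1,000. The split within the 4,500 is not given. Section 6.3.2 suggests 47% Black and 53% Hispanic, which I take as an assumption and vary.
- Australian/White: 14,500 × 0.04775 × 0.95 × 4.25 = 2,795
- Minority at 47% African American: 4,500 × 0.05445 × 0.95 × 4.25 = 989
- Total: about 3,785. At 53% African American it is about 3,805.

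So 19,000 participants yield about 3,787 events under the original mix, and 3,685 under the current one.

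**6. Secondary endpoints.** Solve 19,000 × rate × 4.25 × (1 + HR)/2 = 42.03/(ln HR)² for HR. The amended mix takes 1,000 African American and 500 Hispanic participants (5.26% and 2.63% of 19,000) with the amended U.S. age bands. Dementia in those bands is 0.20×3 + 0.47×6 + 0.19×11 + 0.08×20 + 0.06×37 = 9.33 per 1,000, doubled to 18.66 for African Americans.

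| Endpoint | Mix | Placebo rate per 1,000 | Detectable HR | Stated |
|---|---|---|---|---|
| Dementia | original, 47–53% African American | 12.4–12.5 | 0.806–0.807 | 0.807 |
| Dementia | amended | 11.5 | 0.799 | 0.807 |
| Mortality | original, 47–53% African American | 19.0–19.2 | 0.842 | 0.842 |
| Mortality | amended | 18.6 | 0.840 | 0.842 |

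Appendix 2 gives no Hispanic mortality rate for ages 65–69. I assumed values from 10 (men) and 6 (women) to 20 and 14 per 1,000 before halving; all gave 0.840. With the amended mix, dementia moves to 0.804 at 4.5 years at risk and 0.808 at 4.7 years.

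**The case against.** **The discrepancy is disclosed.** Section 10 points to Appendix 2, which labels its first list as the original assumptions, describes the 2011 change, and states both plans with both powers. This stands in part: the information is in the document. It does not make Section 10 correct, because that section states the old mix as the present plan.

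**3,787 is not an error.** This stands fully. A reader might infer that the number should be replaced by 3,685. It should not be, because it is the right requirement for 90% power whatever the mix. Only its link to what 19,000 participants will deliver is out of date.

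**Section 1.1 is nearly right.** This also stands. It already has the current split, and only its 90% conflicts.

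**Nothing operational is shown to depend on it.** A reader might infer that the DSMB will judge accrual or futility against 3,787. Section 12.3.2 mentions a futility assessment if event rates are lower than expected, but names no event target and leaves formal stopping rules to the Data and Safety Monitoring Plan, which is not at hand.

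**The secondary figures need not come from the old mix.** A reader might infer that 0.807 and 0.842 can arise in no other way. That is too strong. The match depends on an unstated minority split (47% African American gives 0.806 for dementia) and on the time at risk (4.7 years with the amended mix gives 0.808). But those subsections carry over the primary endpoint's assumptions, hence 4.25 years, and at 4.25 years the stated figures fit the original mix and not the amended one.

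**Conclusion.** Section 10 is inconsistent with Appendix 2 and is the passage that is out of date. The statements of 90% power in Section 1.1 and in the Appendix 2 primary-outcome text, and the two-thirds share in the opening of Appendix 2, are leftovers of the same kind. The size is 102 events (2.7%) and 0.8 points of power, resting on the protocol's own rates and 4.25 years at risk.

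This is a small consistency correction. It does not show an underpowered trial, and it calls for no change in sample size. The dementia and mortality hazard ratios are probably stale. The shifts are slight (0.807 to about 0.80, and 0.842 to 0.840), and the amended values depend on inputs the protocol does not fully give.

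**What to change.** 1. **Section 10:** state the 16,500/2,500 split, the amended minority number and the amended age bands including 65–69 (items b and g). Say that 3,787 events are required for 90% power, and that 3,685 are expected, giving 89%.
2. **Section 1.1 and Appendix 2, Primary outcome:** change 90% to 89%. The 90% may stay where it is labelled as belonging to the original plan.
3. **Appendix 2, opening paragraph:** replace the two-thirds share with the achieved one, 16,500/19,000 = about 87%.
4. **Minority number:** call 1,500 expected, not achieved, and reconcile it with Section 6.3.2, where about 70% of 2,500 would be 1,750. The effect is negligible: 250 × (48.9 − 45.4)/1,000 × 4.25 = about 4 events.
5. **Dementia and mortality:** recompute the detectable hazard ratios under the amended mix, and state the minority split, the time at risk and the Hispanic mortality rate for ages 65–69 that were used.

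The cost is a few sentences and numbers. The stated power falls by one point; design, conduct and analysis do not change.

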## **11 ASSESSMENT AND REPORTING OF ADVERSE EVENTS**

### **11.1 Adverse Events**

At the designated intervals for event collection, participants will be asked about specific events of interest as well as any new diseases or conditions.

AEs will be obtained by self-report and will not require supporting documentation. AEs will be reported quarterly to the DSMB and the NIA by blinded treatment group.

### **11.2 Serious Adverse Events (SAE)**

Serious adverse events (SAE) or Serious Adverse Drug Reaction (Serious ADR) are defined as any untoward medical occurrence that:

- is fatal,
- is life-threatening (see below),
- requires in-patient hospitalization or prolongation of existing hospitalization (see below), or
- causes persistent or significant disability / incapacity, or
- is an accidental or intentional overdose.

An SAE is considered life threatening when this places the participant at immediate risk of death from the event as it occurred. A life-threatening event does not include an event that might have caused death had it occurred in a more severe form but that did not create an immediate risk of death as it actually occurred. For example, drug-induced hepatitis that resolved without evidence of hepatic failure would not be considered life threatening, even though drug-induced hepatitis of a more severe nature can be fatal.

A hospitalization is to be considered an SAE only if it is an official admission with a duration of more than 24hr or a minimum of 2 calendar days where exact time of stay is unavailable.

SAEs will be reported from the study sites directly to the DMC within 24 hours of their detection. DMC will compile the details of such events and present the report to the DSMB and the NIA as follows:

1. All final reports of deaths will be provided when available to NIA and a safety monitor.
2. All SAEs shall be reported in a summary format by the blinded treatment arm (A and B) to the DSMB and NIA monthly.

## **12 ADHERENCE TO ETHICAL, REGULATORY AND ADMINISTRATIVE CONSIDERATIONS**

### **12.1 *Ethical Considerations***

#### **12.1.1 *General***

This study will be conducted in accordance with the Declaration of Helsinki 1964 as revised in Edinburgh in 2000 and with the National Health & Medical Research Council Guidelines on Human Experimentation.

In Australia, the Royal Australasian College of General Practitioners Ethics Committee (ethics #NREEC 02/22b), the Monash University Human Research Ethics Committee (IRB00002519; ethics #2006/745MC), the Human Research Ethics Committee (Tasmanian) Network (ethics #H0008933), the Goulburn Valley Health Ethics & Research Committee (Shepparton, ethics #GVH-21/07), ACT Health Human Research Ethics Committee (Canberra, ethics #11/07.997) and The University of Adelaide Human Research Ethics Committee (ethics #H-250-2011) have previously approved the study. In the U.S., individual clinic sites will be responsible for obtaining IRB approval from their respective institutions prior to study initiation. Summary reports of the deliberations of the DSMB will be transmitted to all relevant IRBs and Ethics Review committees

that have approved and are monitoring the study. Study investigators will be responsible for forwarding reports to their relevant IRBs and Ethics Committees.

